**Confidential**

|                         |                                                                                                                                                                                                                                                                                                                                                                                                                                                                                                                                                                                                                                                                                                                                                                                                                                                                                                                                                                                                                                                                                                                                                                                                                                                                                                                  |
|-------------------------|------------------------------------------------------------------------------------------------------------------------------------------------------------------------------------------------------------------------------------------------------------------------------------------------------------------------------------------------------------------------------------------------------------------------------------------------------------------------------------------------------------------------------------------------------------------------------------------------------------------------------------------------------------------------------------------------------------------------------------------------------------------------------------------------------------------------------------------------------------------------------------------------------------------------------------------------------------------------------------------------------------------------------------------------------------------------------------------------------------------------------------------------------------------------------------------------------------------------------------------------------------------------------------------------------------------|
|                         | 
 
○ Chlorzoxazone
 
 
The indication specific exclusion criteria are chosen based on the available data on Acetyl-DL-Leucine of the French Agence nationale de sécurité du médicament et des produits de santé (http://agence-prd.ansm.sante.fr/php/ecodex/notice/N0126720.htm, visited at 24.04.2015, dated on 20.02.2007), in particular hypersensitivity to the agent.
                                                                                                                                                                                                                                                                                                                                                                                                                                                                                                                                                                                                                                                                                                                                                                                                        |
| Trial Procedures | 
Before screening visit/visit 1:
 
 
• Written informed consent
 
 
Treatment period 1: visit 2, 3 and 4
 
Treatment period 2: visit 5, 6 and 7
 
Wash out period of 4 weeks: between visit 4 and 5
 
Follow up/ close-out: visit 8
 
Screening visit/visit 1
 
 
• Check of inclusion/exclusion criteria
 
• Blood test (clinical chemistry: sodium, potassium, creatinine, serum bilirubin level, AST, ALT, urea, ALP, TSH; blood count: hemoglobin, erythrocytes, hematocrit, thrombocytes, leukocytes)
 
• Pregnancy test for women of child bearing potential
 
• Documentation of adverse events
 
• Patient characteristics and medical history as well as medical history concerning the trial specific illness, including frequency of physiotherapy and speech therapy (documented in hours per week)
 
• Drug history including documentation of prior therapies/medications and concomitant medications for treatment of trial specific illness as well as drug history for other indications
 
• Documentation of concomitant medication
 
• Neurological examination
 
• Ataxia rating scale (SARA)
 
 |

Confidential

|  |                                                                                                                                                                                                                                                                                                                                                                                                                                                                                                                                                                                                                                                                                                                                                                                                                                                                                                                                                                                                                                                                                                                                                                                                                                                                                                                                                                                                                                                                                                                                                                                                                                        |
|--|----------------------------------------------------------------------------------------------------------------------------------------------------------------------------------------------------------------------------------------------------------------------------------------------------------------------------------------------------------------------------------------------------------------------------------------------------------------------------------------------------------------------------------------------------------------------------------------------------------------------------------------------------------------------------------------------------------------------------------------------------------------------------------------------------------------------------------------------------------------------------------------------------------------------------------------------------------------------------------------------------------------------------------------------------------------------------------------------------------------------------------------------------------------------------------------------------------------------------------------------------------------------------------------------------------------------------------------------------------------------------------------------------------------------------------------------------------------------------------------------------------------------------------------------------------------------------------------------------------------------------------------|
|  | 
Visit 2 and 5 (start of treatment period)
 
 
• Randomization (at visit 2)
 
• Dispensing of trial drug
 
• Ataxia rating scales (SARA, SCAFI)
 
• Self-administered questionnaires (EQ-5D-5L, BDI-II, FSS)
 
• Documentation of adverse events
 
• Documentation of frequency of physiotherapy and speech therapy (hours per week)
 
• Documentation of concomitant medications
 
• Blood test (clinical chemistry: sodium, potassium, creatinine, serum bilirubin level, AST, ALT, urea, ALP, TSH; blood count: hemoglobin, erythrocytes, hematocrit, thrombocytes, leukocytes) (only at visit 5)
 
• Pregnancy test for women of child bearing potential (only at visit 5)
 
 
Visit 3, 4, 6, 7 and visit 8 (follow-up)
 
 
• Ataxia rating scales (SARA, SCAFI)
 
• Quality of life questionnaires (EQ-5D-5L, BDI-II, FSS)
 
• Documentation of adverse events
 
• Documentation of frequency of physiotherapy and speech therapy (hours per week)
 
• Documentation of concomitant medication
 
• Blood test (clinical chemistry: sodium, potassium, creatinine, serum bilirubin level, AST, ALT, urea, ALP, TSH; blood count: hemoglobin, erythrocytes, hematocrit, thrombocytes, leukocytes) (at visit 4 and 7)
 
• Pregnancy test for women of child bearing potential (visit 4 and 7)
 
• Return of trial drug at visit 4 and 7
 
• Compliance check at visit 3, 4, 6 and 7
 
 |
|--|----------------------------------------------------------------------------------------------------------------------------------------------------------------------------------------------------------------------------------------------------------------------------------------------------------------------------------------------------------------------------------------------------------------------------------------------------------------------------------------------------------------------------------------------------------------------------------------------------------------------------------------------------------------------------------------------------------------------------------------------------------------------------------------------------------------------------------------------------------------------------------------------------------------------------------------------------------------------------------------------------------------------------------------------------------------------------------------------------------------------------------------------------------------------------------------------------------------------------------------------------------------------------------------------------------------------------------------------------------------------------------------------------------------------------------------------------------------------------------------------------------------------------------------------------------------------------------------------------------------------------------------|

Confidential

|                                    |                                                                                                                                                                                                                                                                                                                                                                                                                                                                                                                                                                                                                                                                                                                                                                                                                                                                                                                                                                                                                                                                                                                                                                                                                                                                                                                                                                                                                                                                                                                                                                                                                                                                                                                                                                                                                                                                                                                                                 |
|------------------------------------|-------------------------------------------------------------------------------------------------------------------------------------------------------------------------------------------------------------------------------------------------------------------------------------------------------------------------------------------------------------------------------------------------------------------------------------------------------------------------------------------------------------------------------------------------------------------------------------------------------------------------------------------------------------------------------------------------------------------------------------------------------------------------------------------------------------------------------------------------------------------------------------------------------------------------------------------------------------------------------------------------------------------------------------------------------------------------------------------------------------------------------------------------------------------------------------------------------------------------------------------------------------------------------------------------------------------------------------------------------------------------------------------------------------------------------------------------------------------------------------------------------------------------------------------------------------------------------------------------------------------------------------------------------------------------------------------------------------------------------------------------------------------------------------------------------------------------------------------------------------------------------------------------------------------------------------------------|
| Trial Specific Measurements | 
 
• Ataxia scores (SARA, SCAFI)
 
• Self-administered questionnaires (FSS, BDI-II, EQ-5D-5L)
 
• Blood tests including pregnancy tests
 
                                                                                                                                                                                                                                                                                                                                                                                                                                                                                                                                                                                                                                                                                                                                                                                                                                                                                                                                                                                                                                                                                                                                                                                                                                                                                                                                                                                                                                                                                                                                                                                                                                                                                                                                            |
| Investigational Trial Sites | This is a multi-center, international trial with 7 investigational trial sites in Europe planned at the time of finalization of the protocol.                                                                                                                                                                                                                                                                                                                                                                                                                                                                                                                                                                                                                                                                                                                                                                                                                                                                                                                                                                                                                                                                                                                                                                                                                                                                                                                                                                                                                                                                                                                                                                                                                                                                                                                                                                                                   |
| Statistical Rationale       | 
Efficacy:
 
The efficacy of the experimental intervention will be determined by testing and estimating differences regarding the absolute change in SARA total score measured at the 2-week visit and at the end of the verum/ placebo period compared to period-level baseline at visit 2 (treatment period 1) and at visit 5 (treatment period 2)
 
Description of the primary efficacy and population:
 
To analyze the differences in SARA total score between both treatments, a linear mixed effects model for DeltaSARA for the absolute change in SARA total score will be performed (fixed effects: factors for treatment visit, treatment-by-visit interaction, mean of both period-level baseline SARA total scores as covariate; patient-specific random intercepts).
 
The primary efficacy analysis will be performed according to the intention-to-treat (ITT) principle. Sensitivity analyses to assess robustness of trial results include multiple imputation techniques for the missing primary outcome. The significance level is <math>\alpha = 5\%</math>.
 
Safety:
 
Data about adverse events will be descriptively analyzed by verum and placebo phase.
 
Secondary endpoints:
 
The confirmatory analysis extends to the key secondary endpoint EQ-5D-5L if a benefit in the primary analysis could be demonstrated. Then this analysis will also be based on the ITT principle. Further secondary endpoints are the subscores of SARA and SCAFI, BDI-II, and FSS, which are not considered in the hierarchical multiple testing procedures and therefore will be analyzed descriptively (mainly by the Wilcoxon signed rank test where considered appropriate). The corresponding confidence intervals for treatment group effects will be reported. Change scores will be assessed at the 6-week visit at the end of the verum/ placebo
 |

Confidential

|                      |                                                                                                                                                                                                                                                                                                                                                                                                                                                                                                                                                                                                                                                                                          |
|----------------------|------------------------------------------------------------------------------------------------------------------------------------------------------------------------------------------------------------------------------------------------------------------------------------------------------------------------------------------------------------------------------------------------------------------------------------------------------------------------------------------------------------------------------------------------------------------------------------------------------------------------------------------------------------------------------------------|
|                      | treatment period, and at the follow-up visit 8.                                                                                                                                                                                                                                                                                                                                                                                                                                                                                                                                                                                                                                          |
| Time Schedule | 
Per Subject:
 
Twenty weeks in total, including 2 x 6 weeks of verum/placebo treatment, 4 weeks wash-out between both treatment periods and a follow-up visit 4 weeks after last IMP intake. Patients receiving prohibited medication (see exclusion criteria) at visit 1 have to perform 4 weeks of wash-out prior to randomization.
 
Trial duration:
 
 
• Recruitment period (months): 16
 
• Planned Start Date (FPFV): 01.12.2015
 
• Planned End Date (LPLV): 01.08.2017
 
• First patient in to last patient out (months): 20
 
 
Duration of the entire trial (months): 32
 |

**Date and version identifier**Revision Chronology:

|            |                       |
|------------|-----------------------|
| 04.09.2015 | Original Version V1.0 |
|------------|-----------------------|

## 2 Schedule of Activities and Assessments

A delay of -3 and +5 days is acceptable for visit 2 and 5, for all other visits a delay of  $\pm 5$  days is acceptable.

|                                                        | Enrollment |                       | Treatment period 1 |                             |                             |                      | Treatment period 2 |                             |                             | Close-out                             |
|--------------------------------------------------------|------------|-----------------------|--------------------|-----------------------------|-----------------------------|----------------------|--------------------|-----------------------------|-----------------------------|---------------------------------------|
|                                                        | Before     | Screening
Visit 1♦ | Visit 2            | Visit 3
2 weeks after V2 | Visit 4
6 weeks after V2 | Wash-out:
4 weeks | Visit 5            | Visit 6
2 weeks after V5 | Visit 7
6 weeks after V5 | Follow-up Visit 8
4 weeks after V7 |
| Timeline (days)                                 |            | 0/-28                 | 0                  | 14                          | 42                          | 70                   | 70                 | 84                          | 112                         | 140                                   |
| Informed consent                           | X          |                       |                    |                             |                             |                      |                    |                             |                             |                                       |
| Inclusion / exclusion criteria                         |            | X                     |                    |                             |                             |                      |                    |                             |                             |                                       |
| Patient history, demographics                          |            | X                     |                    |                             |                             |                      |                    |                             |                             |                                       |
| Documentation of physiotherapy/speech therapy          |            | X                     | X      | X                           | X                           |                      | X                  | X                           | X                           | X                                     |
| Neurological examination                               |            | X                     |                    |                             |                             |                      |                    |                             |                             |                                       |
| Blood tests                                            |            | X*                    |                    |                             | X*                          |                      | X*                 |                             | X*                          |                                       |
| Randomization                                          |            |                       | X                  |                             |                             |                      |                    |                             |                             |                                       |
| Dispensing of trial drug                               |            |                       | X                  |                             |                             |                      | X                  |                             |                             |                                       |
| Return of trial drug                                   |            |                       |                    |                             | X                           |                      |                    |                             | X                           |                                       |
| Compliance check                                       |            |                       |                    | X                           | X                           |                      |                    | X                           | X                           |                                       |
| Patient questionnaires (EQ-5D-5L, BDI-II, FSS)         |            |                       | X                  | X                           | X                           |                      | X                  | X                           | X                           | X                                     |
| Ataxia rating scale: SARA                              |            | X                     | X      | X                           | X                           |                      | X                  | X                           | X                           | X                                     |
| Ataxia rating scale: SCAFI                             |            |                       | X                  | X                           | X                           |                      | X                  | X                           | X                           | X                                     |
| Documentation of (S)AE                                 |            | X                     | X      | X                           | X                           |                      | X                  | X                           | X                           | X                                     |
| Documentation of concomitant medication (drug history) |            |                       | X                  | X                           | X                           |                      | X                  | X                           | X                           | X                                     |

 prior to first study specific intervention

 if visit 1 and visit 2 take place at the same time, ataxia rating scale (SARA), documentation of physiotherapy/speech therapy and documentation of (S)AE are assessed only once

♦ if patients are on medication due to cerebellar symptoms at visit 1, there is a planned 4-week-wash-out between visit 1 and 2 prior to randomization. Otherwise visit 1 and visit 2 should take place at the same time.

\* incl. negative pregnancy test for women of child bearing potential

Confidential

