**10.2.3 Wash out**

A wash out period of 4 weeks will be performed between the two treatment periods (between visit 4 and 5)

#### 10.2.4 Treatment period 2

The treatment period 2 will start after a wash out period of 4 weeks (between visit 4 and visit 5) and will include 3 visits from week 10 to week 16.

A delay of -3 and +5 days is acceptable for visit 5, for all other visits a delay of  $\pm 5$  days is acceptable.

All visits will be performed according to the Schedule of Activities and Assessments (see 2).

##### Visit 5

- Dispensing of trial drug
- Ataxia rating scales (SARA, SCAFI)
- Self-administered questionnaires (EQ-5D-5L, BDI-II, FSS)
- Documentation of adverse events
- Documentation of frequency of physiotherapy and speech therapy (hours per week)
- Documentation of concomitant medication
- Blood test including pregnancy test for women of child bearing potential pregnancy test for women of child bearing potential

Visit 5 takes place after the wash-out period of 4 weeks.

##### Visit 6 and visit 7

- Ataxia rating scales (SARA, SCAFI)
- Self-administered questionnaires (EQ-5D-5L, BDI-II, FSS)
- Documentation of adverse events
- Documentation of frequency of physiotherapy and speech therapy (hours per week)
- Documentation of concomitant medication
- Blood test including pregnancy test for women of child bearing potential (only at visit 7)
- Documentation of concomitant medication
- Return of trial drug at visit 7
- Compliance check

Visit 6 takes place after two weeks on medication, visit 7 after 6 weeks on medication.

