## **11.6 Pregnancy**

Women of childbearing potential are required to have a negative pregnancy test to exclude a pregnancy before being randomized in the clinical trial.

Pregnancy testing will be conducted at the time points specified in the schedule of activities (see 2).

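### Wash-out patients get their eligibility check and blood and pregnancy tests only at visit 1, about 28 days before first dispensing, and the -3-day window for visit 2 does not fit the 4-week drug criterion

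*Protocol*

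**What the plan says.** The footnote to the schedule in section 2 states that "if patients are on medication due to cerebellar symptoms at visit 1, there is a planned 4-week-wash-out" between visits 1 and 2. For everyone else it adds: "Otherwise visit 1 and visit 2 should take place at the same time". The timeline row accordingly gives visit 1 as day 0 or day -28. Randomization and first dispensing are at visit 2.

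- **Eligibility check.** The row "Inclusion / exclusion criteria" is marked at visit 1 only, and the visit 2 list in section 10.2.2 contains no such check.
- **Tests.** Blood tests, which include the pregnancy test, are marked at visits 1, 4, 5 and 7. The synopsis lists visits 2 and 5 together and restricts both tests to the later one: "Pregnancy test for women of child bearing potential (only at visit 5)". Section 10.2.4 lists "Blood test including pregnancy test for women of child bearing potential" at visit 5. Section 10.1.3 lets a routine sample up to 7 days old replace the visit 1 blood test.
- **Pregnancy rule.** Section 11.6 says "Women of childbearing potential are required to have a negative pregnancy test to exclude a pregnancy before being randomized in the clinical trial", and then: "Pregnancy testing will be conducted at the time points specified in the schedule of activities".
- **Window.** Section 2 says "A delay of -3 and +5 days is acceptable for visit 2 and 5", and section 10.2.2 repeats this for visit 2.
- **Drug criterion.** Sections 8.2 and 8.3 bar the listed drugs within 4 weeks before randomization. The synopsis and section 10.2.1 require a wash-out of 4 weeks.

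**The concern.** Two things fixed for the wash-out path fit badly with the rest of the protocol.

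First, the only scheduled eligibility check falls on a day when a patient still taking a listed drug cannot yet meet the drug criterion. The tests meant to exclude pregnancy and liver failure (AST/ALT above 300 U/l, section 8.3) are about four weeks old when the first drug is handed out. A pregnancy or a raised transaminase that arises during the wash-out would first be tested for at visit 4, once the patient has been through the titration and about four weeks at 5 g per day.

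Second, a site can hold visit 2 inside its permitted window and still randomize a patient who does not satisfy sections 8.2 and 8.3.

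What is at stake is patient safety in a subgroup and clean eligibility rules, not the treatment estimate.

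**Working it through.** This is calendar arithmetic. The one assumption is that the visit 2 window is counted from visit 1 plus 28 days, the only anchor the schedule offers.

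**The plan's own figure.** Section 10.2.1 gives a total duration of 24 weeks with the wash-out: 4 + 6 + 4 + 6 + 4 = 24. It reproduces.

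**Inputs.** Wash-out 28 days; visit 2 window -3/+5 days; visit 4 at 42 ± 5 days after visit 2 (all section 2); reusable blood sample up to 7 days before visit 1 (section 10.1.3).

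**Age of check and tests at first dispensing, and time to the next tests**

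| Interval | Wash-out patient | Visits 1 and 2 on the same day |
|---|---|---|
| Eligibility check and tests to dispensing, planned | 28 days | 0 days |
| Same, with window | 28 - 3 = 25 to 28 + 5 = 33 days | 0 days |
| Blood sample taken 7 days before visit 1 | 25 + 7 = 32 to 33 + 7 = 40 days | 7 days |
| Visit 1 tests to visit 4 tests, planned | 28 + 42 = 70 days | 42 days |
| Same, with windows | 25 + 37 = 62 to 33 + 47 = 80 days | 37 to 47 days |

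**Comparison within the protocol.** The break between periods is also 28 days (day 42 to day 70). There, both tests are done at visit 4 and again at visit 5, where drug is next dispensed. Section 10.1.3 also rates a blood sample from 8 to 30 days before visit 1 as a minor violation. So for a same-day patient a 25-day-old sample at dispensing is a violation, while for a wash-out patient a sample of 25 to 33 days is on schedule.

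**Window against criterion.** Visit 2 at -3, -2 or -1 days falls 25, 26 or 27 days after visit 1. With last intake on the day of visit 1, the drug-free interval is at most 3 days short: 28 - 25 = 3, and 3/28 = 10.7%. If the drug was stopped at least 3 days before visit 1, day 25 complies.

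**After the change.** With a 0/+5 window the interval is 28 to 33 days and the earliest date meets the criterion. With the check and tests repeated at visit 2, their age at dispensing is 0 days.

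**Number of patients.** The protocol gives none. Purely for scale, an assumed 10% to 30% of the 108 randomized would be 11 to 32 patients (10.8 to 32.4), and fewer for the pregnancy test. The point does not rest on this share.

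**The case against.** The strongest reply is that the gate already exists. Section 10.2.1 requires all subjects to be screened before randomization and only eligible ones to be allocated, and concomitant medication is recorded at visit 2. A visit tolerance does not override an exclusion criterion. All of this stands. A reader might infer from the window that the protocol permits ineligible patients to be randomized. It does not: the window merely accepts a date that the criterion may forbid.

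On the tests, section 11.6 sets no maximum age, so a negative test at visit 1 meets its letter. Section 8.3 requires reliable contraception, so few pregnancies are to be expected. Visit 5 follows exposure to trial drug and may be tested for that reason too. This also stands, and it keeps the point small. But exposure in period 1 is already followed by tests at visit 4, so the visit 5 repeat works at least partly as a check before new drug is given, and visit 2 has no counterpart.

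Sections 7.2 and 10.2.2 say only that the two visits can coincide in unmedicated patients, so an early or later visit 2 may not be confined to wash-out patients. That is a reason to word the fix by visit date.

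Stronger consequences are tempting but unsupported:

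- **Withdrawal.** Section 13.5 says violations do not justify withdrawing a subject, and section 16.2.2 only allows withdrawal, with this case under medical indication.
- **Loss from the per-protocol analysis.** Section 13.4 speaks of major violations, a shortfall of at most 3 days is unlikely to be judged major, and that analysis is only a sensitivity analysis.
- **A missing laboratory baseline.** Section 13.1 plans descriptive adverse event analyses and states no laboratory comparison that would need one.

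**Conclusion.** The point holds and is minor. In wash-out patients the eligibility check and the blood and pregnancy tests are scheduled 28 days (25 to 33) before first dispensing, and the next tests come about 6 weeks into treatment. The schedule, the synopsis and the visit list in section 10.2.2 agree on this, so it is not a slip in one table. The visit 2 window is inconsistent with the 4-week criterion by up to 3 days for a patient who took a listed drug up to visit 1, and the criterion prevails. The conclusion rests on counting the window from visit 1 plus 28 days. It concerns a subgroup whose size the protocol does not give, and no effect on the SARA comparison is claimed.

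**What to change.** In section 2, the synopsis and section 10.2.2, for any patient whose visit 2 is not on the same day as visit 1:

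1. Confirm the criteria of sections 8.2 and 8.3 at visit 2 and repeat the routine blood test and, where applicable, the pregnancy test, with results known before randomization and dispensing.
2. Set the visit 2 window to 0/+5 days, and define the earliest date as at least 28 days after the last intake of any drug listed in section 8.3.

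Cost per patient: one more routine sample and possibly one pregnancy test. Section 10.1.3 gives about 20 ml in total over 4 scheduled samples, so 20/4 = 5 ml each and about 25 ml in total for these patients. Sites lose 3 days of scheduling slack. The tests are ones the trial already runs, in each centre's own laboratory.
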